
#### Study 2: the study of medical records

First, the anonymized data will be collected using a list of 32 predefined items (see Additional file 1: Table S1), some of which are similar to the variables used in the registry study. These data will then be aggregated and presented descriptively. In the second step, the data will be compared with analogous data from all centres included in the study to identify regional differences. Finally, the analysis will be made by comparing this data with corresponding samples gathered from the general population as well as the ongoing H2020 projects REALMENT (grant agreement No. 964874) and TIMESPAN (grant agreement No. 96538). The aim is to identify differences between the study population and the general population.

#### Study 3: the exploratory clinical study

Following the sign of informed consent, we will assess at baseline, the distribution of all possible combinations of the 5 MetS criteria (32 dispositions with repetition of two elements) among BD patients. A subject scoring positive at 3 criteria out of 5 will be defined as MetS + . At baseline, MetS + subjects will be compared to MetS—(less than 3 out of 5 criteria) for 15 predefined items, using either t-test for independent samples (continuous items) or Fisher Exact test (for binary items). Due to test multiplicity, individual tests p-value will be adjusted using Benjamini–Hochberg procedure.

The evolution in MetS status (MetS + /MetS−) from baseline to 1 year follow-up will be evaluated using multistate models, in order to identify what items might affect the transition probabilities. The 5 MetS criteria combinations will be explored using multiple correspondence analyses in order to identify possible clusters based on the predefined items. All the analyses will be performed using R (R Foundation, version 4.3.1 or newer). All tests will be two-sided.

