
**Table 1 Tab1:** Diagnostic criteria for MetS as agreed in the Consensus Statement published in Alberti et al., 2009

Diagnostic criteria	Threshold values
Waist circumference	≥ 102 cm (M); ≥ 88 cm (F)
Fasting plasma glucose	≥ 100 mg/dL or specific treatment
Blood pressure	≥ 130/85 mmHg or specific treatment
Triglycerides	≥ 150 mg/dL or specific treatment
HDL cholesterol	< 40 mg/dL (M); < 50 mg/dL (F) or specific treatment

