#### Study 3: the Exploratory Clinical Study (ECS)

##### Participants

Study 3 consists of the ECS conducted in five countries (France, Italy, Germany, Norway, and Spain), with a total of 11 recruiting sites (Additional file 1: Table S2). A total of 400 participants, aged 18–65 years, diagnosed with either BD I or BD II or BD not otherwise specified (NOS) according to the DSM-5, will be enrolled: these participants will be selected from patients with BD who have had at least one contact with the mental health service in the past year. Table 3 shows the inclusion and exclusion criteria. To ensure a representative sample of patients with BD, a specific stratification will be employed, according to the following schema: age will be split into two strata (18–45 and 46–65 years), sex will be split into two strata (male and female) and age of onset (before 21 years and after 21 years) will be used as a proxy of disorder severity.

**Table 3 Tab3:** Inclusion and exclusion criteria for the ECS

Inclusion criteria	Exclusion criteria
Age 18–65 years	Plan to relocate in the subsequent year
Primary diagnosis of BD I or BD II or BD NOS	Severe psychiatric comorbidities (schizophrenia spectrum disorders)
At least one contact with the mental health service in the last year	Severe cognitive impairment
Signed informed consent	Severe substance/alcohol misuse as quantified by specific scores on the Alcohol Use Disorders Identification Test (AUDIT) (Babor et al. 2001) and the Drug Abuse Screening Test (DAST) (Skinner 1982)

The study foresees 2 evaluation times: the first at the entry into the study (T0) and the second after 1 year (T1).

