#### Study 3: the exploratory clinical study

We estimated the sample size based on planned comparisons for 15 variables of interest (Table 6) for a two independent groups design (MetS + vs MetS−) assuming an expected proportion of Mets (at least three criteria out of five) of approximately 31%. With the estimated cohort of 400 subjects (180 Mets + , 220 Mets−), assuming a power of at least 80% and a significance level of 0.002 (to account for test multiplicity), we are going to be able to identify, at baseline, a significant effect size (ES) of 0.4 for independent t-tests (continuous variables) or an ES of 0.395 for a comparison of two independent proportions (assuming normal asymptotic test).

**Table 6 Tab6:** List of variables to be used for power calculation in the ECS at baseline

Sex	1. Female, male
Age	1. 18–45 years, 46–65 years
Marital status	1. Married, unmarried
Children (yes/no)	1. Yes, 2. No
Education years, mean (SD)	1. 0–10, > 10
Current occupational status	1. Employed, 2. Unemployed
Age of first contact with mental health services (Years), Mean (SD)	Continuous variable
Bipolar disorder I or II or NOS	1. Yes, 2. No
Comorbidity with other mental disorders	1. Yes, 2. No
Lifetime substance or alcohol use disorder	1. Yes, 2. No
Ever treated with lithium or mood stabilizers	1. Yes, 2. No
Ever treated with antipsychotics	1. Yes, 2. No
Number of diagnoses of MC lifetime assessed with Elixhauser	Continuous variable range 0–32
Body mass index	Continuous variable
Family history of diabetes and/or CVD	1. Yes, 2. No

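### Study 3 baseline comparisons: one of the 15 items cannot vary as coded, age and education are listed as two classes, and the tests carry no term for strata, site or country

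*Protocol article*

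**What the plan says.** The analysis section for Study 3 compares MetS+ with MetS− patients at baseline on 15 predefined items, "using either t-test for independent samples (continuous items) or Fisher Exact test (for binary items"). It adds that "individual tests p-value will be adjusted using Benjamini–Hochberg procedure" and that "All tests will be two-sided". It names no covariate, stratum, site or country term for these tests.

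The only list of 15 items in the article is Table 6, in the sample-size section for Study 3, where it is presented as the list for the power calculation. Three of its rows matter here:

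- "Bipolar disorder I or II or NOS" is coded 1 = Yes, 2 = No.
- Age is coded "18–45 years, 46–65 years".
- Years of education is labelled as a mean with SD but coded 0–10 against more than 10.

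Table 3 (Participants) lists "Primary diagnosis of BD I or BD II or BD NOS" among the inclusion criteria. Under Participants and Recruitment strategy, patients are drawn at random within strata of age, sex and age of onset, at 11 sites in five countries. The power statement uses 180 vs 220 patients, 80% power and "a significance level of 0.002 (to account for test multiplicity"), and gives detectable effects of 0.4 (t-test) and 0.395 (two proportions).

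**The concern.** The baseline comparison is meant to describe how bipolar patients with MetS differ from those without, and the project's stated aims include risk factors. Three features weaken it.

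First, a comparison whose item takes one value in the whole sample gives no result. Bipolar subtype, a clinically obvious candidate, would then go unexamined.

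Second, cutting a measured variable in two discards information, and the power statement has almost no margin above 80% to absorb the loss.

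Third, the age, sex and onset mix of the sample is set by design, and patients come from five health systems. A crude difference in, say, antipsychotic exposure or employment may therefore partly reflect who was sampled where. A reader looking for risk factors could take it for more than that.

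**Working it through.** **1. The diagnosis item.** Table 3 requires BD I, BD II or BD NOS. Table 6 asks Yes/No to the same three diagnoses. At the planned group sizes the table is 180 Yes / 0 No (MetS+) against 220 Yes / 0 No (MetS−). With an empty margin only one table is possible, so Fisher's test gives p = 1 and the odds ratio is undefined. The same holds for any other group sizes.

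The effect on the other 14 items is small. The article gives no Benjamini–Hochberg level; assuming 0.05, the smallest step is 0.05/15 = 0.00333 with the item and 0.05/14 = 0.00357 without it.

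If subtype was intended, the item has three levels, and the analysis section provides tests only for continuous and binary items.

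**2. Two-class coding of age and education.** The plan's own figures come first, with n₁ = 180, n₂ = 220 and two-sided alpha 0.002:

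- Detectable effect (normal) = (z₀.₉₉₉ + z₀.₈₀) × √(1/180 + 1/220) = (3.090 + 0.842) × 0.1005 = 0.395. The t-based value is 0.398. The stated 0.395 and 0.4 reproduce.
- Power at 0.4 SD: 0.4 × √(180 × 220/400) = 3.980, and Φ(3.980 − 3.090) = 81.3%. With the noncentral t it is 80.7%.

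Now take a normal trait with a true shift of 0.4 SD and cut it at a point c that leaves a share p₂ of the MetS− group above it. Then p₁ = 1 − Φ(c − 0.4). Power = Φ{[(p₁ − p₂) − 3.090 × SE₀]/SE₁}, with SE₀ pooled and SE₁ unpooled. The share of information kept is φ(c)²/[p₂(1 − p₂)].

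| Share above cut, MetS− | MetS+ share | Information kept | Power, 180 vs 220 | Power, 124 vs 276 |
|---|---|---|---|---|
| not cut | – | 100% | 80.7% | 72.2% |
| 50% | 65.5% | 64% | 51.4% | 41.8% |
| 30% | 45.0% | 58% | 50.6% | 43.6% |
| 20% | 32.9% | 49% | 44.1% | 39.2% |

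The last column uses the split implied by the stated 31% MetS proportion (0.31 × 400 = 124). The article's 180 of 400 is 45%, a separate inconsistency shown here only as a sensitivity check. The article gives no distribution of age or education, so both the normal shape and the cut positions are assumptions.

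**3. Crude tests.** The documents give no MetS or exposure rates by stratum or country, so the distortion can only be illustrated. Take two equal strata with MetS rates m₁, m₂ averaging 31%, exposure rates q₁, q₂, and no association within either stratum. Exposure is then (m₁q₁ + m₂q₂)/(m₁ + m₂) in MetS+, and [(1 − m₁)q₁ + (1 − m₂)q₂]/[(1 − m₁) + (1 − m₂)] in MetS−. For the middle row below these are 0.328/0.62 = 52.9% and 0.672/1.38 = 48.7%.

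| MetS rates (assumed) | Exposure rates (assumed) | Exposure MetS+ vs MetS− | Crude OR | Rejection in direction of bias, alpha 0.002, 124 vs 276 |
|---|---|---|---|---|
| 26% / 36% | 45% / 55% | 50.8% vs 49.6% | 1.05 | 0.2% |
| 22% / 40% | 40% / 60% | 52.9% vs 48.7% | 1.18 | 1.0% |
| 15% / 47% | 30% / 70% | 60.3% vs 45.4% | 1.83 | 37.1% |

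The nominal one-direction rate is 0.1%. The effect of crude testing therefore runs from negligible to material, depending on rates the article does not give.

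**The case against.** The study is called exploratory, and its stated primary aim concerns associations among the five MetS criteria, not these 15 tests. A t-test or Fisher test is a valid test of a crude association. The analysis section makes no causal claim for the baseline results and uses multistate models to ask which items affect transitions. Age and sex are themselves among the 15 items, and supplementary adjusted analyses may sit in an analysis plan that is not shown. All of this stands. A reader might infer that the 15 comparisons are confounded; the documents support only that they may be, and only if read as more than crude description. The multistate models, however, address change over one year and do not replace an adjusted look at the baseline profile.

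Table 6 is a power-calculation table, and the education label points towards a continuous variable. So the two-class analysis of age and education is a likely inference, not a stated fact, and the power loss is conditional on it.

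A reader might also infer that BMI must leave the tested family because "Waist circumference" is a MetS criterion. BMI itself is not a criterion, waist is one of five, and any three suffice. The overlap is real and deserves a note, but removing BMI is a matter of preference. Nor is there a case that a near-certain item seriously loosens the correction: with BMI alone, the next step at level 0.05 is 2/15 × 0.05 = 0.0067, which is how the procedure is meant to work.

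None of this rescues the diagnosis item as coded. The registry list in Table 2 has a similar row without Yes/No coding, which suggests that subtype was intended.

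**Conclusion.** The point holds in three parts of differing certainty.

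- **Certain:** as coded, one of the 15 comparisons can give no result. If subtype was meant, the plan names no test for it. The cost to the other items is negligible.
- **Conditional on the analysis following Table 6:** for age and education, power for a true 0.4 SD difference falls from about 81% to about 44–51% at 180 vs 220 and alpha 0.002, assuming a normal trait and a cut between 50/50 and 80/20. The three items listed as continuous (age at first contact, Elixhauser count, BMI) are unaffected.
- **As written, but of unknown size:** the tests ignore the sampling strata, site and country, so the differences are crude. The odds ratios of 1.05 to 1.83 rest wholly on assumed rates and show only a possible range.

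This should be corrected, but it does not invalidate the baseline analysis as a description.

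**What to change.** 1. Recode the diagnosis item as BD I / BD II / BD NOS and test it with a Fisher–Freeman–Halton or likelihood-ratio test.
2. State that age and years of education are analysed as continuous, and correct Table 6 to match.
3. Label the t and Fisher results as crude. For each item add a logistic model for MetS+ adjusted for age, sex, onset stratum and country or site. Leave out the adjuster that is the item itself, and do not adjust age at first contact for onset stratum, which measures nearly the same thing. Apply Benjamini–Hochberg to the adjusted p-values.
4. Keep BMI in the family if wished, with a note that it overlaps with the waist criterion.

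The cost is wording and some extra modelling, with no new data. With 124 MetS+ patients, a model with a one-parameter item, age, sex, onset stratum and four country terms has 8 parameters, or 124/8 = 15.5 events each. Ten fixed site terms instead would give 14 parameters and 124/14 = 8.9, so country terms or a random site intercept are easier to support. The adjusted estimate also answers a different question from the two-group comparison behind the power calculation, and the plan should say so.

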### Power and sample size

#### Study 1: the registry study

To determine the required sample size for fitting a Cox proportional hazards model, recent guidelines were followed (Riley et al. 2019). With an estimated cohort of 40,000 incident patients with BD and an expected 12,000 outcome events based on a 31% prevalence rate (Engin 2017) the minimum required sample size was estimated to be 4,199 individuals for a model with 24 candidate predictors. This assumed an average 2-year follow-up, a shrinking factor of 0.90, and an anticipated R2 of 0.05. For the ML models, sample size calculations based on statistical power are not directly applicable, since these techniques focus on optimizing predictive performance (i.e., reducing a loss function) rather than hypothesis testing. Instead, sample size and model complexity will be considered when training (e.g., learning curves plots by sample size and several parameters).

With a large cohort of 40,000 patients, our study is adequately powered to develop and validate robust predictive models for MetS in patients with BD using both standard survival analysis and ML techniques. This will allow the identification of modest predictive effects across a range of candidate variables and the construction of accurate predictive models for MetS incidence in this population (Engin 2017; Peduzzi et al. 1995).

#### Study 2: the study of medical records

Considering a confidence level of 95% and a standard error of 5%, the study would require the inclusion of at least 385 patients to provide a valid representation of the population under investigation. However, our study takes on an additional layer of complexity as we aim to make a cross-country comparison, analysing differences within the study population. To accomplish this and maintain robust statistical power, we need to consider a power level of 0.9 and an alpha level of 0.05. These choices are essential to ensure that our study is adequately powered to detect any meaningful differences between the countries being examined. Given these criteria and assuming an effect strength (η2) of 0.015, we should aim to include a minimum of 346 patient records from each site, thus totalling 1,730 patient records for the four countries comparative analysis (France, Germany, Italy, Norway, and Spain). This larger sample size is necessary to account for the population differences and to draw meaningful conclusions about the healthcare conditions and outcomes in each country.

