**Methods:**

The BIPCOM project aims to investigate MC, specifically MetS, in individuals with BD using various approaches. Initially, prevalence rates, characteristics, genetic and non-genetic risk factors, and the natural progression of MetS among individuals with BD will be assessed by analysing Nordic registers, biobanks, and existing patient datasets from 11 European recruiting centres across 5 countries. Subsequently, a clinical study involving 400 participants from these sites will be conducted to examine the clinical profiles and incidence of specific MetS risk factors over 1 year. Baseline assessments, 1-year follow-ups, biomarker analyses, and physical activity measurements with wearable biosensors, and focus groups will be performed. Using this comprehensive data, a CST will be developed to enhance the prevention, early detection, and personalized treatment of MC in BD, by incorporating clinical, biological, sex and genetic information. This protocol will highlight the study's methodology.

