#### Study 2: the study of medical records

BIPCOM offers a unique opportunity to gather and analyse extensive datasets from patients with BD utilizing local medical services across five countries. All centres participating to this project use electronic patient records: an ad hoc Medical Record Abstraction Tool (MRAT) will be employed to extract clinical data and information related to 32 predefined variables (Additional file 1: Table S1), including past and current comorbidities and treatments, and a set of biomarkers related to MetS. Patients with BD will be randomly selected from those with inpatient or outpatient visits, aiming for a total sample size of at least 1,500 patients (300 per site). Rigorous measures will be taken to minimize selection bias and ensure data quality, following Jansen's guidelines (Jansen et al. 2005), which involve cross-verification with source documents, close collaboration with local physicians, written guidelines for data collectors, interobserver studies for training, regular data collector meetings, and random checks of completed MRATs against original medical records. Consent is not required as the data used are fully anonymized clinical routine data. MRAT will capture information on various medical comorbidities, including MetS, diabetes mellitus, dyslipidaemias, obesity, endocrine imbalances, CVD, other significant comorbidities, and concurrent prescribed drug use.

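### Study 2 sizes its cross-country comparison as if records were independent, so the stated power of 0.9 and the country-level conclusions make no allowance for centre

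*Protocol article*

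**What the plan says.** The abstract describes the source of the records as "existing patient datasets from 11 European recruiting centres across 5 countries". The design section for Study 2 adds that every participating centre holds electronic records, and gives the target as "aiming for a total sample size of at least 1,500 patients (300 per site".

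The Study 2 part of the power section makes the country the unit of interest. Its inputs are "we need to consider a power level of 0.9 and an alpha level of 0.05" and "assuming an effect strength (η2) of 0.015", and its result is "a minimum of 346 patient records from each site, thus totalling 1,730 patient records". It says these choices "ensure that our study is adequately powered to detect any meaningful differences between the countries being examined" and that the larger sample is needed to "draw meaningful conclusions about the healthcare conditions and outcomes in each country". It mentions no centre level, intraclass correlation or design effect.

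The same paragraph gives 385 as the minimum for a valid representation of the population, at 95% confidence and what it calls a 5% standard error.

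The Study 2 analysis section plans a descriptive presentation, after which "the data will be compared with analogous data from all centres included in the study to identify regional differences". It names no test or model.

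**The concern.** Records from one centre share a case mix, prescribing habits and ways of recording, so they resemble each other more than records from different centres do. When the question is about countries and each country is represented by about two centres, the difference between two country means carries centre-to-centre variation. A sample size built on independent records leaves that variation out.

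Two things are at stake. The article's power statement is unconditional, and readers will rely on it. The article also promises conclusions about each country, yet the data may show no more than that the participating centres differ. The conflict between 1,500 and 1,730 records, and the reference to four countries where five are listed, are separate matters. This point remains at either sample size.

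**Working it through.** **Inputs from the article.** Alpha 0.05, power 0.9, η² = 0.015, 346 per site and 1,730 in total (Study 2 power section); 11 centres in 5 countries (abstract). Since 5 × 346 = 1,730 and 5 × 300 = 1,500, the per-site counts use site to mean country.

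**Inputs assumed.** The article gives no ICC; the range used is 0.001 to 0.05. The division of records among centres is not shown; an even spread gives m = 1,730/11 ≈ 157.3 per centre.

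**Step 1: reproduce 346.** f² = η²/(1 − η²) = 0.015/0.985 = 0.01523. Power comes from the noncentral F distribution with noncentrality N·f², for independent records.
- Two groups: 345 each gives 0.8992 and 346 each gives 0.9000. The match is exact.
- Five groups: 204 each (1,020 in total) gives 0.901. With N = 1,730, power is 0.992.

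So 346 is a pairwise, two-country size multiplied by five. It holds no slack on the pairwise basis and no allowance for clustering.

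**Step 2: allow for centre.** Design effect = 1 + (m − 1)·ICC; effective records per country = 346/design effect. Power is recomputed at the effective size.

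| ICC | Design effect | Effective n per country | Pairwise power | Five-country omnibus power |
|---|---|---|---|---|
| 0 | 1.00 | 346 | 0.90 | 0.992 |
| 0.001 | 1.16 | 299 | 0.85 | 0.98 |
| 0.005 | 1.78 | 194 | 0.68 | 0.89 |
| 0.01 | 2.56 | 135 | 0.52 | 0.73 |
| 0.02 | 4.13 | 84 | 0.36 | 0.49 |
| 0.05 | 8.81 | 39 | 0.19 | 0.24 |

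The omnibus test tolerates a design effect of 1,730/1,020 = 1.696, which is an ICC of 0.696/156.3 ≈ 0.0045. These figures use the design effect alone and ignore the loss from having few centres, so they are on the favourable side.

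**Step 3: would more records per centre help?** With c centres per country, effective n cannot exceed c/ICC. At c = 11/5 = 2.2 the ceiling is 220, 110 and 44 at ICC 0.01, 0.02 and 0.05, against the 346 needed pairwise. Above an ICC of 2.2/346 ≈ 0.006, no number of records from these centres restores the pairwise 0.9.

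**Step 4: what if the test ignores centre?** I simulated the five-country F test on records, with 346 per country, no true country effect, and 11 centres split 3/2/2/2/2 or 3/3/2/2/1. At ICC 0 the false-positive rate is about 5%, as it should be. At 0.001, 0.005, 0.01, 0.02 and 0.05 it is about 8–9%, 26–29%, 45–50%, 69–72% and 91%. For one pair of countries, 2·[1 − Φ(1.96/√design effect)] gives 0.07, 0.14, 0.22, 0.34 and 0.51.

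**Step 5: what if the test respects centre?** A centre-level F test (4 and 6 df, 3/2/2/2/2 split) has a false-positive rate of 0.05 to 0.06. Its power at η² 0.015 is 0.81 at ICC 0, 0.41 at 0.01 and 0.15 at 0.05. The 0.81 at ICC 0 is the price of few degrees of freedom, so not all of the shortfall from 0.9 is due to clustering.

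**Step 6: the 385.** 1.96² × 0.25/0.05² ≈ 384.1, rounded up to 385. The 0.05 is therefore the 95% margin of error under simple random sampling. A standard error of 5 points would need 0.25/0.05² = 100 records; at 385 the standard error is √(0.25/385) = 2.55 points.

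**The case against.** The strongest reply is that the article names no test for Study 2. Its analysis section is mainly descriptive and speaks of comparing centres, and an analysis plan not shown may well model centre. This stands. A reader might infer that Study 2 will declare ordinary centre variation to be a country difference; the article does not support that, because the false-positive rates in Step 4 apply only if the comparison follows the independence basis of the sizing.

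A reader might also infer that the study suffers inflated false positives and lost power together. It does not: ignoring centre inflates alpha, and respecting centre costs power. These belong to different analyses.

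Three further points are fair:
- The ICC and the centre split are assumptions, and at an ICC of 0.001 the loss is small (0.90 to 0.85).
- Read as a five-country omnibus test, 1,730 records have a reserve that absorbs a small ICC.
- For pooled prevalence, clustering need not defeat the 5-point target. With 1,500 records in 11 centres, m ≈ 136.4 and the design effect at ICC 0.01 is 2.35, so the half-width near 50% is 1.96·√(0.25 × 2.35/1,500) ≈ 3.9 points. At ICC 0.05 the design effect is 7.77 and the half-width 7.1 points.

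None of this rescues the power statement. The article itself states the 0.9, and 346 yields it pairwise only with independent records; a model chosen later cannot make that figure true. If the aim is only to describe differences among the participating centres, the clustering argument loses its force, but then the promise of conclusions about each country has to go.

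**Conclusion.** The point holds in a limited form. The 346 per country reproduces exactly as an independent-records, two-group size, while the article draws its patient datasets from 11 centres in 5 countries. On that pairwise basis any positive ICC takes power below the stated 0.9. How far below depends on an ICC that the article does not give: the loss is slight at 0.001, close to half at 0.01, and leaves little power at 0.05.

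The choice of analysis decides which consequence follows, and the article leaves that choice open. The division of records among the 11 centres is also unclear. If Study 2 has a single data source per country, country and centre cannot be separated at all, and a test ignoring centre would have simulated false-positive rates of about 49%, 72% and 98% at ICC 0.005, 0.01 and 0.05.

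The label on 385 is a small, separate error in the same paragraph: it is a margin of error, not a standard error.

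**What to change.** - Keep the centre code in the anonymised extract. Settle this before extraction, since it may not be recoverable afterwards.
- Compare countries with a linear or logistic mixed model: country fixed, centre random, small-sample degrees of freedom.
- Where a country has one data source, or if Study 2 has only one per country, report differences between participating centres and not between countries.
- State that the 0.9 holds only for independent records, and give a range over assumed ICCs with the number of centres per country; otherwise drop it.
- Limit the closing sentence on conclusions in each country to the participating centres.
- Give pooled prevalence with confidence intervals that allow for centre.
- Restate 385 as the simple-random-sample size for a 5-point 95% margin of error.

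The cost is wording, one random effect and one retained variable; no further records are needed. The downside is that the stated power and the reach of the country-level conclusions become less favourable.

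### Study 2 has two incompatible record targets (300 and 346 per site), and 346 is the size for one unadjusted comparison of two countries, not for a five-country test

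*Protocol article*

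**What the plan says.** Under Study design, the Study 2 paragraph describes records from five countries, "aiming for a total sample size of at least 1,500 patients (300 per site". Since 1,500/300 = 5, site here means country, although the project has 11 recruiting centres.

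Under Power and sample size, the Study 2 paragraph works in two steps.

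- A precision step, "Considering a confidence level of 95% and a standard error of 5" per cent, which gives 385 patients.
- A comparison step: "we need to consider a power level of 0.9 and an alpha level of 0.05", so that the study is "adequately powered to detect any meaningful differences between the countries being examined". Then, "assuming an effect strength (η2) of 0.015", it requires "a minimum of 346 patient records from each site, thus totalling 1,730 patient records for the four countries comparative analysis". The parenthesis that follows lists France, Germany, Italy, Norway and Spain. The next sentence calls the larger sample necessary.

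Under Data analyses, the Study 2 data are first presented descriptively and then "compared with analogous data from all centres included in the study to identify regional differences". The article nowhere reconciles 300 with 346 per site.

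**The concern.** Three statements do not fit together. The design target is smaller than the minimum that the power paragraph calls necessary. The same sentence says four countries, lists five and multiplies by five. And the per-site figure is much larger than a test across four or five groups would need at the stated effect size, which suggests that it was derived for a different comparison.

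At stake is what the 90% means. A reader who takes it as the power of the country comparison cannot tell whether 300 per country is more than enough or slightly too few. The answer differs between an omnibus test and a comparison of two countries.

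**Working it through.** **Inputs**, all from the Study 2 power paragraph unless noted: η² = 0.015; alpha = 0.05; power = 0.90; 346 per site; 1,730 in total. From the Study 2 design paragraph: 300 per site; 1,500 in total; five countries. Sidedness is not stated for Study 2; an F test on η² with two groups equals a two-sided t-test.

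**Step 1: the totals.** 346 × 5 = 1,730, while 346 × 4 = 1,384. The stated total therefore uses five countries, not four. Gap to the design target: 346 − 300 = 46 per site (46/346 = 13%), and 1,730 − 1,500 = 230 in total.

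**Step 2: effect size.** f² = η²/(1 − η²) = 0.015/0.985 = 0.01523, so f = 0.1234. For two equal groups, d = 2f = 0.2468.

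**Step 3: reproduce 346.** One-way ANOVA with k equal groups of n has noncentrality λ = k·n·f². Power is the probability that a noncentral F with k − 1 and k·n − k degrees of freedom exceeds the 5% critical value. The smallest n per group for 90% power is:

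| k | n per group | total |
|---|---|---|
| 2 | 346 | 692 |
| 3 | 278 | 834 |
| 4 | 234 | 936 |
| 5 | 204 | 1,020 |
| 11 | 124 | 1,364 |

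Of these, only k = 2 gives 346. There the power is 0.8992 at n = 345 and 0.9000 at n = 346. The plan's 1,730 is thus a two-group size multiplied by five.

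**Step 4: power at the two targets, alpha 0.05.**

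| Comparison | 300 per country | 346 per country |
|---|---|---|
| Five-country omnibus, η² = 0.015 across the five (λ = 1,500 × 0.01523 = 22.8; 1,730 × 0.01523 = 26.3) | 98.1% | 99.2% |
| One unadjusted pair, d = 0.2468 (λ = 600 × 0.01523 = 9.14; 692 × 0.01523 = 10.54) | 85.5% | 90.0% |

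The two rows read η² = 0.015 differently: across five countries in the first, between two in the second.

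**Step 5: the 385.** With p = 0.5, a 95% confidence interval with half-width 0.05 needs 1.96² × 0.25/0.05² = 384.2, hence 385. A standard error of 0.05 would need 0.25/0.05² = 100. The 385 therefore rests on a 5% margin of error.

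**The case against.** The best defence is that the stated aim is to detect any meaningful difference between countries. Sizing each country so that any one pair has 90% power, then multiplying by five, is coherent and gives exactly 346 and 1,730. On that reading the 90% is correct for each unadjusted pair. On the omnibus reading 90% is exceeded at both targets. This stands: at 1,730 the power claim is unlabelled rather than false. It does not remove the lower design target or the four/five slip.

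The design target is also a floor (at least 1,500), which 1,730 satisfies. That stands too. A reader might infer that sites will stop at 300, but the article does not say so. What remains is that the floor lies below a minimum described as necessary.

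A reader might further infer that pairwise power is really about 58%. That is the result at 300 per country for d = 0.247 with a Bonferroni alpha of 0.05/10 = 0.005. The article specifies neither that adjustment nor that effect for every pair. Set beside the 98%, the figure mixes two meanings of η². If 0.015 is the effect across five equal countries, the most separated pair has d between 2f·5/√24 = 0.252 (two countries against three) and f·√10 = 0.390 (two extremes, the rest central). Its power at alpha 0.005 and 300 per country, with pooled variance, then runs from about 61% to 97.5%. No single pairwise figure follows from the plan's inputs.

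The missing name of the test and the missing multiplicity rule are matters that an article may leave to the analysis plan, and they are not part of this point.

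**Conclusion.** The point holds as a contradiction in the stated sample size and an unlabelled power claim. The design target is 13% per site below the stated minimum, and the number of countries contradicts itself within one sentence. The 346 is the size for one unadjusted two-country comparison; a five-country omnibus test with the same inputs needs about 204 per country.

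A reader might conclude that Study 2 is underpowered. The documents do not support that: both totals exceed the 1,020 needed for the omnibus test. The only shortfall that follows from the stated inputs is 85.5% against 90%, for a single unadjusted pair at 300 per country.

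These figures assume equal country sizes, independent records and a continuous outcome; clustering of centres within countries was not modelled. The pairwise figures read η² = 0.015 as a two-country effect, which is the reading that reproduces 346.

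The standard-error wording is a minor slip, since 385 does not set the final size. Overall this should be corrected, but it does not threaten the study.

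**What to change.** Use one target in both Study 2 paragraphs, write five countries, and say which comparison the power refers to. Either target can be kept.

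- **If 1,500 (300 per country) is kept:** drop 346 as a minimum. Restate the power either as about 98% for the five-country omnibus test at η² = 0.015 across countries, or as about 85% for a single unadjusted pair at d = 0.247. Say which reading of η² applies.
- **If 1,730 (346 per country) is kept:** correct the design paragraph, and say that 90% applies to a single unadjusted comparison of two countries.

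Do not print 58% beside the omnibus figure unless its own assumptions (d = 0.247 for the pair, Bonferroni alpha 0.005) stand with it. Replace standard error by margin of error (half-width of the 95% confidence interval) for the 385.

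Cost: wording only if 1,500 is kept, with a lower pairwise power on the page. Keeping 1,730 commits the study to 230 more existing records than the present floor of 1,500.
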